**Fig. 2 Fig2:**
[figure not shown]
The timepoint of study period

### Dietary intake and physical activity assessment

To ensure lack of change in dietary intakes and physical activity of participants throughout the study, they will be asked to record their dietary intakes and physical activity in a day every two weeks. Therefore, all patients will complete six dietary records and six physical activity records (two for weekends and four for weekdays) during the study. All records would be reviewed immediately and possible problems will be resolved by interview. We will compute nutrient intake of study participants bases on the analysis of these dietary records. The software we will use for this computation is Nutritionist 4, in which the database was modified for Iranian foods. To analyze physical activity records, we will use MET-h/day values for each physical activity, based on published guidelines [18], considering the time spent by each participant .

### Anthropometric assessment

Data on anthropometric indices, including body weight, height, WC, and BMI will be obtained at study baseline and end of the trial. Body weight will be measured in a fasting state, without shoes and wearing light clothing to the nearest 0.1 kg accuracy, using a weighing calibrated scale (Seca, Hamburg, Germany). Height will be measured by mounted tape, without shoes and at a standing position near to the wall to the nearest 0.1 cm accuracy using a stadiometer (Seca, Hamburg, Germany). WC will be measured to the nearest 0.1 cm accuracy by non-stretching tape measure around the abdomen. BMI will be calculated by dividing weight in kilograms by height in meters squared.

### Blood sampling, biochemical, and molecular measurements

In a fasting state, a 10-mL venous blood sample will be taken from each patient between 07:00 and 09:00 hours. The samples will be immediately centrifuged at 20 °C, 3000 rpm for 10 min in aseptic condition. Serum samples will be separated in RNAase free micro-tubes in the clean room, where all equipment will be UV exposed for 20 min. Then the samples will be stored at − 70 °C. Serum lipid profiles (TC, HDL, LDL, TG), liver markers (ALT, AST, total, direct and indirect bilirubin), glucose, and calcium levels will be measured by the enzymatic colorimetric method using commercial kits. Serum insulin, vitamin D, VDR, laminin, collagen type IV, and hyaluronic acid will be measured using an enzyme-linked immunosorbent assay (ELISA) kit. Insulin resistance and insulin sensitivity will be determined using the HOMA-IR and QUICKI equations, respectively [19].

The gene expression of serum MiRs (MiR-122, MiR-21, and MiR-34a) will be determined by real-time polymerase chain reaction (PCR).

### Statistical analysis

Statistical analyses of all data will be performed using SPSS software version 21.0 (SPSS Inc., Chicago, IL, USA). The intention-to-treat approach will be used for data analysis. Data will be expressed as mean ± standard deviations (±SD). The one-sample Kolmogorov–Smirnov test will be used for assessing the normality of the distribution of data. In case of non-normal distribution of a variable, we will apply the log transformation. If the variables were non-normally distributed even, after log transformation, we will use non-parametric tests in the analyses. Repeated measure analysis of variance will be used to identify the effect of the intervention of outcome variables. In these analyses, baseline levels of the outcome variables will be considered as covariates. If any outcome variable was non-normally distributed, we will use the Friedman test. *P* < 0.05 will be considered statistically significant. All analyses will be done by a blind researcher before uncoding the study interventions.

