## Methods/design

### Participants

This parallel randomized double-blind placebo-controlled clinical trial (RCT) will be done on patients with NASH. Patients will be recruited from the Masoud Internal Specialized Clinic and Imam Khomeini Hospital, affiliated with Tehran University of Medical Sciences, Tehran, Iran. We calculated required sample size based on data from a previous study [12] by considering serum laminin as a key dependent variable, type I error of 0.05, and study power of 90%. Considering the mean difference in serum laminin levels of 136.7 ng/mL between the two groups [12], based on the suggested formula for parallel clinical trials, we reached the sample size of 18 patients in each group. Taking into account a possible drop-out rate of 30%, 23 patients will be enrolled in each group. The study is registered in the Iranian Registry of Clinical Trials website (http://www.irct.ir, identifier: IRCT201405251485N13). This study was reported based on recommended check lists for clinical trials (Additional files 1 and 2).

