### Outcomes

The primary outcomes of the present clinical trial would be serum VDRs, laminin, collagen type IV, hyaluronic acid, MiR-122, MiR-21, and MiR-34a. The secondary outcomes would be liver enzymes, total, direct, and indirect bilirubin, lipid profile, and glycemic indices. We will also examine serum vitamin D and calcium concentrations. All these measurements will be assessed at study baseline and at the end of the trial. Vitamin D supplementation will be considered for the placebo group as post-trial care (Fig. 2).

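### Intention-to-treat is promised, but the named two-time-point methods use only patients with both samples, so about 32 of 46 would be analysed if the 30% drop-out allowance were used up without final samples

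*Protocol article*

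**What the plan says.** All references are to the protocol article.

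- **Statistical analysis**, analysis set: "The intention-to-treat approach will be used for data analysis".
- **Statistical analysis**, method: "Repeated measure analysis of variance will be used to identify the effect of the intervention of outcome variables". It adds that "In these analyses, baseline levels of the outcome variables will be considered as covariates", and as fallback that "If any outcome variable was non-normally distributed, we will use the Friedman test". The software is SPSS 21.
- **Outcomes**, on the seven primary outcomes and the rest: "All these measurements will be assessed at study baseline and at the end of the trial". The week-6 contact, under Intervention, is described only as the collection of the second set of bottles.
- **Participants**, sample size on serum laminin: "we reached the sample size of 18 patients in each group". Then: "Taking into account a possible drop-out rate of 30%, 23 patients will be enrolled in each group".

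**The concern.** Intention-to-treat means that every randomised patient counts in the comparison, in the arm assigned. In its usual SPSS form, repeated-measures ANOVA deletes any patient who lacks one of the repeated values, and the Friedman test likewise needs a complete set per patient. With one baseline and one final value, a patient without the final value contributes nothing to either method. The sample-size text points the same way: it enlarges 18 to 23 per group because drop-outs are treated as lost from the analysis.

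So the article does more than leave a missing-data rule unwritten. It fixes an analysis set, and then fixes methods that do not deliver that set by themselves. If the missing patients differ from those who stay, and differ by arm, the comparison loses the protection of randomisation while its label says otherwise.

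**Working it through.** **Inputs from the article.** 18 evaluable and 23 enrolled per group, 46 in total; drop-out allowance 30%; laminin difference 136.7 ng/mL; type I error 0.05; power 90%.

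**Assumptions, not in the article.** Two-sided test; laminin SD (back-solved below); correlation between baseline and final value r = 0.3, 0.5 or 0.7; the strength and pattern of informative drop-out in step 4.

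**1. The plan's own enrolment figure.** 18 × 1.30 = 23.4, which gives the stated 23 when the fraction is dropped. (Dividing instead, 18 / 0.70 = 25.7, would give 26. That is a separate matter.)

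**2. Patients with both samples if 30% give no final one.** 23 × 0.70 = 16.1 per group and 46 × 0.70 = 32.2 in total. About 32 patients are analysed and about 14 are left out.

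**3. Implied SD.** A two-sided t-test with 18 per group and 90% power needs a standardised difference of 1.112, so SD = 136.7 / 1.112 = 122.9 ng/mL. The normal approximation gives 123.0 to 126.5.

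**4. Bias if drop-out is informative in one arm.** Suppose there is no true effect and placebo drop-out is random. In the vitamin D arm, the 7 of 23 who leave are those highest on a score that correlates 0.5 with the end-of-trial residual (high laminin being worse).

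- Share retained: 16/23 = 0.696, so the normal cut-point is z = 0.512, with density 0.350.
- Mean shift of the score among those retained: 0.350 / 0.696 = 0.503 SD.
- Shift of the residual: 0.5 × 0.503 = 0.252 residual SDs.
- Residual SD = 122.9 × √(1 − r²). Standard error with 16 per group = residual SD × √(2/16).

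| r | Residual SD (ng/mL) | False benefit (ng/mL) | Standard error (ng/mL) | Ratio |
|---|---|---|---|---|
| 0.3 | 117.2 | 29.5 | 41.4 | 0.71 |
| 0.5 | 106.4 | 26.8 | 37.6 | 0.71 |
| 0.7 | 87.8 | 22.1 | 31.0 | 0.71 |

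Rejection under no effect is P(Z > 1.96 − 0.71) + P(Z < −1.96 − 0.71), about 0.106 + 0.004 = 0.11.

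Simulations of the baseline-adjusted comparison (2,000 to 4,000 trials per setting) agree: false benefit about 21 to 30 ng/mL, rejection about 10 to 12%. With final values from all 46 patients, rejection returns to about 5 to 6%.

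**5. Random drop-out.** With a true difference of 136.7 ng/mL, the completers estimate is 136.0 to 137.2 ng/mL, so there is no bias. The cost is power: at r = 0.3, about 86 to 88% with 32 patients against about 96 to 97% with all 46.

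**6. Does imputation repair step 4?** Multiple imputation within arm from baseline left the bias where it was: in one run −26.7/−26.5/−20.7 ng/mL, against −26.9/−26.8/−20.8 for completers at r = 0.3/0.5/0.7. Rejection was about 9 to 10%, against 10 to 12%. Imputing from baseline reproduces what the completers already show.

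**The case against.** The strongest reply is that this is an article condensed from a fuller protocol, and that missing-data rules and follow-up after stopping tablets commonly sit in documents not shown. Their absence is no error. Intention-to-treat followed by repeated-measures ANOVA on imputed data would also be coherent. Both statements stand. A reader might infer that the analysis set and the method flatly contradict each other; the text does not support that, because filling in values first would remove the conflict. What remains is that the two choices the article does make, applied as written, do not deliver the stated property.

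Two other strong readings should be resisted. A reader might infer that the plan expects 30% to leave, but the article gives 30% only as a possible rate used to enlarge the sample. A reader might also infer that leavers have no final sample. The article nowhere says so: Outcomes does not restrict the end-of-trial measurement to patients still on tablets. The figure of 32 is therefore conditional.

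It is also fair to say that the 10 to 12% error rate comes from a constructed case, and that nothing in the article suggests such drop-out. The case shows how large the exposure could be; it does not predict it. Finally, a baseline-adjusted comparison of week-12 values also omits patients without a final value, so changing the model alone repairs nothing.

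The Exclusion criteria section removes randomised patients for events after entry, including weight loss. That is a further tension with intention-to-treat and needs its own reconciliation; it neither replaces this point nor is needed for it.

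**Conclusion.** The concern holds in conditional form. Unless missing values are filled in first, the named methods analyse only patients with both samples, which is not what the intention-to-treat statement promises. If the full 30% allowance were used up and leavers gave no final sample, about 14 of 46 randomised patients would drop out of every primary comparison.

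With random drop-out the result is unbiased, with less power than all 46 would give. Under the assumed drop-out in the vitamin D arm only (correlation 0.5 with the end-of-trial residual, SD about 123 ng/mL, r from 0.3 to 0.7), the false benefit is about 20 to 30 ng/mL and the error rate about 10 to 12% instead of 5%. These sizes rest on assumptions that the article neither states nor excludes.

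A reader might infer that multiple imputation would settle the matter. On baseline information alone it would not; in these checks, what restores the error rate is having the final samples. The point should be dealt with, at medium confidence.

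**What to change.** 1. **Adherence and Outcomes:** state that the planned week-12 sample is still sought from every randomised patient who stops the tablets or misses visits, and that it is analysed in the randomised arm.
2. **Statistical analysis:** compare all available week-12 values between arms, adjusted for baseline.
3. **Statistical analysis:** add one sensitivity analysis that makes the missing vitamin D values progressively worse and reports where the conclusion changes.
4. **Label:** if patients without a final value are left out, call the result a completers analysis and not intention-to-treat. If multiple imputation from baseline is used, do not present it as removing bias from informative drop-out.

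The cost is wording, reminder calls, some extra analysis, and a less favourable label if samples are not obtained. No new patients, visits or assays are needed beyond those planned. Timing limits the first item. Trial status expected recruitment to end by 15 January 2019 and the article appeared on 4 March 2019, so many leavers' week-12 dates had probably passed by publication. For them, only the sensitivity analysis and the label remain.

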### Randomization

Forty-six patients will be enrolled in the whole project. We will use block randomization, in which the assignment will be done based on sex (male/female) and BMI (overweight/obese). Participants will be matched based on sex and BMI into blocks. Therefore, the block size would be four [14, 15]. This method of randomization will provide the equal number of men and women as well as overweight and obese patients that will be assigned to the intervention and placebo groups [14, 15]. Random allocation sequence will be generated using Random Allocation Software: RAS [16]. Given the total sample size of 46 and considering matched cases in terms of sex and BMI, the sample size in each subgroup of gender and BMI will be 12 ± 1. The allocation process of participants into vitamin D and placebo groups will be carried out using computer-generated random sequences by a third person who will not be involved in the project directly.

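### Allocation is blocked on sex and BMI class, but the stated model adjusts only for the baseline outcome; the two-visit repeated-measures form also leaves the effect estimate open to misreading

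*Protocol article*

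**What the plan says.** Randomization section: "We will use block randomization, in which the assignment will be done based on sex (male/female) and BMI (overweight/obese"). On block size it adds: "Therefore, the block size would be four". It also expects that "the sample size in each subgroup of gender and BMI will be 12 ± 1". I read this as four sex-by-BMI strata with permuted blocks of four inside each.

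Outcomes section, after listing the primary and secondary outcomes: "All these measurements will be assessed at study baseline and at the end of the trial". Each outcome therefore has two values per patient, and only one of them is post-baseline.

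Statistical analysis section: "Repeated measure analysis of variance will be used to identify the effect of the intervention of outcome variables". The next sentence is "In these analyses, baseline levels of the outcome variables will be considered as covariates". Sex and BMI class are not named in the model, and the section does not say which term of the repeated-measures analysis is the treatment effect.

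**The concern.** Two features of the stated model do not fit the design.

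First, blocking within sex-by-BMI strata removes most chance imbalance in those factors between arms, so the treatment estimate varies less from trial to trial. A model without the factors still counts their variance as error. If they carry prognostic information beyond baseline, the reported standard error is larger than the true one, the interval is too wide, and some of the precision gained by blocking goes unused. With 46 patients enrolled and drop-out allowed for, precision is worth keeping.

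Second, baseline enters twice: as one of the two repeated measurements and as the covariate. The group main effect then averages over a visit at which treatment cannot have acted. Anyone who reports that term as the treatment effect would state it at half its size.

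**Working it through.** **Inputs from the article.** Four strata, blocks of four, about 12 patients per stratum, 46 in total (12 + 12 + 11 + 11 = 46). Two measurement times. Baseline value as covariate. Laminin difference 136.7 ng/mL, type I error 0.05, power 90%, 18 per group before drop-out.

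**Assumed, because the article does not give them.** Two-sided test; baseline to week-12 correlation 0.5; additive sex and BMI effects of equal size; complete data. R² is the share of the week-12 variance left after baseline that sex and BMI explain. The article gives no value, so a range is shown.

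**Step 1. The planned effect in SD units.** The article gives no SD for laminin, so its 18 per group cannot be reproduced directly. Solving n = 2(1.960 + 1.282)² / d² for d at n = 18 gives d = 3.242 × √(2/18) = 1.08, so SD = 136.7 / 1.08 ≈ 126.5 ng/mL. Allowing for rounding up to 18, the SD lies between about 123 and 126.5, and d between 136.7 / 126.5 = 1.08 and 136.7 / 123 = 1.11.

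**Step 2. Standard error and type I error.** With exact balance, the true variance of the estimate is proportional to 1 − R², while the baseline-only model estimates something close to the full residual variance. The ratio of model SE to true SE is then about 1/√(1 − R²): 1/√0.90 = 1.054 at R² = 0.10 and 1/√0.80 = 1.118 at R² = 0.20. Simulation of the actual block scheme (8,000 null trials per row) agrees:

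| R² | SE ratio, baseline only | Type I error, baseline only |
|---|---|---|
| 0 | 1.000 | 4.8% |
| 0.02 | 1.011 | 4.6% |
| 0.05 | 1.026 | 4.3% |
| 0.10 | 1.053 | 3.7% |
| 0.20 | 1.115 | 2.8% |
| 0.30 | 1.188 | 1.9% |

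With sex and BMI class in the model, the ratio is 1.000 and the type I error 4.7% in every row.

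**Step 3. Power, baseline only against adjusted** (4,000 trials per cell):

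| Effect, patients analysed | R² = 0.10 | R² = 0.20 | R² = 0.30 |
|---|---|---|---|
| 1.09 SD, 46 | 98.9% / 99.1% | 99.0% / 99.5% | 99.4% / 99.9% |
| 1.09 SD, 36 | 95.6% / 96.2% | 96.3% / 97.8% | 96.6% / 98.9% |
| 0.86 SD, 46 | 91.1% / 92.8% | 92.2% / 95.4% | 93.3% / 97.1% |
| 0.70 SD, 46 | 76% / 79% | 77% / 83% | 78% / 88% |

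The first two rows use the effect implied by Step 1; the last two are assumed smaller effects. At R² = 0 adjustment gains nothing and costs almost nothing (90.1% against 89.7% at 0.86 SD).

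**Step 4. The repeated-measures form.** Let Y0 and Y1 be the two values, and let ANCOVA be Y1 = a + b·arm + c·Y0 + e.

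- Group main effect: this models (Y0 + Y1)/2 = a/2 + (b/2)·arm + ((1 + c)/2)·Y0 + e/2. Estimate and SE are both halved.
- Time-by-group term: this models Y1 − Y0 = a + b·arm + (c − 1)·Y0 + e. Estimate and SE equal those of ANCOVA.

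One simulated data set with 23 per arm shows this:

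| Term | Estimate | SE | F |
|---|---|---|---|
| ANCOVA | −119.63 | 25.68 | 21.70 |
| Group main effect | −59.81 | 12.84 | 21.70 |
| Time by group | −119.63 | 25.68 | 21.70 |

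The P value is the same in all three; only the size of the group term differs.

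**The case against.** The best defence has four parts.

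1. A reader might infer that the standard errors will be too large. The article does not support that as a flat statement. It holds only if sex and BMI class add to what baseline already explains, and the article gives no figure for this. At R² of 0.05 or less the overstatement is under 3%. This objection stands, and the point is conditional for that reason.

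2. A reader might infer that the benefit of blocking is thrown away, or that power suffers badly. Neither follows. Balance on sex and BMI is kept whatever the model, and baseline-only power itself rises slightly with R². Gains as large as 78% to 88% need an effect of 0.7 SD, which the article does not state, together with the top of the assumed R² range. For laminin, the one outcome with a planning effect, the gain is about 0 to 2 points. The error is conservative, so false positives are not inflated. This stands too.

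3. A reader might infer that the plan will report half the treatment effect. It does not say so. It names neither the group term nor the time-by-group term, the time-by-group term gives the full effect, and the test is identical. The halving is a reporting risk, not a stated error.

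4. This is a condensed article, and a fuller plan may list more covariates. That has some force, but the article does more than stay silent: it states the model and its covariate, and leaves out the factors on which it allocates. Recommending a better stated model is therefore fair.

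**Conclusion.** The mismatch between allocation factors and model is in the text. Its consequence is a possible loss of precision of unknown size, in the conservative direction: none at R² = 0, a standard error about 5% too large at 0.10 and about 12% at 0.20, with type I error about 3.7% and 2.8%. The power gain from adjusting is small at the implied laminin effect and larger for outcomes with smaller effects, for which the article gives no planning figures. The repeated-measures form is valid as a test but gives two candidate estimates that differ by a factor of two, and the article does not choose between them. These sizes rest on the assumptions listed in the check and on reading the scheme as four strata with blocks of four. This is a low-cost improvement and not a threat to the validity of the trial.

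**What to change.** Replace the repeated-measures sentence and the covariate sentence that follows it with: *The week-12 value of each outcome will be analysed by ANCOVA with arm, baseline value, sex and BMI class (the randomisation factors) as terms. The adjusted week-12 difference between arms, with its 95% CI, is the effect estimate.*

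Sex and BMI class are already needed for allocation, so no new data are required. The cost is two degrees of freedom and one sentence. The article has the analyses done before the codes are broken, so the change can be made without knowledge of the arms, provided it is recorded before then.

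### The named non-parametric fallback, the Friedman test, tests change over time and not vitamin D against placebo

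*Protocol article*

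**What the plan says.** The Participants section fixes the design: "This parallel randomized double-blind placebo-controlled clinical trial (RCT) will be done on patients with NASH". The Outcomes section lists seven primary outcomes: "The primary outcomes of the present clinical trial would be serum VDRs, laminin, collagen type IV, hyaluronic acid, MiR-122, MiR-21, and MiR-34a". It gives each of them two time points: "All these measurements will be assessed at study baseline and at the end of the trial".

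The Statistical analysis section states the main method and its purpose, "Repeated measure analysis of variance will be used to identify the effect of the intervention of outcome variables", and adds "In these analyses, baseline levels of the outcome variables will be considered as covariates". It then describes the route away from that method twice. The first description puts log transformation before any switch: "If the variables were non-normally distributed even, after log transformation, we will use non-parametric tests in the analyses". The second, after the main method, names the test and does not mention the log step: "If any outcome variable was non-normally distributed, we will use the Friedman test". No other non-parametric test is named in the article.

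**The concern.** The fallback stands in for an analysis whose declared purpose is to estimate the effect of the intervention, so it has to compare the randomised arms. The Friedman test compares related measurements within the same patients. With a baseline and a week-12 value per patient, it asks whether values moved. It does not ask whether they moved differently under vitamin D and placebo.

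The error can go either way. A change shared by both arms (regression to the mean, season, assay drift, the effect of being in a trial) could be reported as an effect of vitamin D. A real difference made of opposite movements could be missed.

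**Working it through.** **Inputs from the article.** Two parallel arms; k = 2 measurements per patient; 23 enrolled and 18 evaluable planned per arm; 30% drop-out; significance at 0.05 (taken as two-sided, since the article does not say). Applying the drop-out rate to enrolment gives 23 × 0.70 = 16.1, hence 16 completers per arm in the main illustration.

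**Assumed, because the article gives no figure.** The correlation ρ between baseline and week 12 on the log scale (0.6, with 0.5 as an alternative), and the common drift d in SD units (0 to 0.5).

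**Step 1: what the statistic contains.** For n patients, Q = 12/[n·k·(k+1)] × ΣRⱼ² − 3n(k+1). With k = 2, let s be the number of patients whose value rises (no ties). The rank sums are R₁ = 2n − s and R₂ = n + s. Then

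Q = (2/n)(R₁² + R₂²) − 9n = (2s − n)²/n.

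Only s and n enter. Neither treatment arm nor the size of the baseline value does. This needs none of the assumptions above.

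**Step 2: can the test be arranged to compare the arms?**
- Pooled over both arms, it tests time.
- Run within each arm, it gives two P values and no comparison between them.
- Using the randomisation blocks as Friedman blocks would need one observation per treatment in each block. The Randomization section has blocks of four patients for two arms, and the Friedman sentence offers the test as the substitute for the repeated-measures analysis.

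**Step 3: size of the error once the path is reached.** The chance that one patient rises is p = Φ(d/√[2(1 − ρ)]). With ρ = 0.6 the denominator is √0.8 = 0.894. For n = 32, Q exceeds 3.84 when s ≤ 10 or s ≥ 22. Binomial probabilities with no treatment effect are:

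| Common drift (SD) | p | Pooled Friedman rejects | Exactly one arm significant |
|---|---|---|---|
| 0 | 0.500 | 5% | 14% |
| 0.2 | 0.588 | 17% | 26% |
| 0.5 | 0.712 | 70% | 50% |

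At ρ = 0.5, the 70% becomes 60%.

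Now let the arms move 0.5 SD in opposite directions, a true difference of 1 SD. Then p is 0.712 in one arm and 0.288 in the other, the expected s is 16 of 32, and the pooled test rejects in about 3%.

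**Step 4: other sample sizes and a between-arm test.** Simulation of 20,000 trials per setting at ρ = 0.5 gave:

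| Setting | Pooled Friedman, 18 / 23 per arm | Mann-Whitney on change, 18 / 23 per arm |
|---|---|---|
| Both arms fall 0.5 SD, no treatment effect | 70.3% / 77.5% | 4.6% / 4.8% |
| Arms move 0.5 SD in opposite directions | 4.5% / 3.8% | 80.5% / 89.5% |

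At 16 per arm and ρ = 0.6, rank analysis of covariance rejects in about 5% under a common 0.5 SD drift and has about 92% to 93% power for a 1.08 SD effect. That effect is itself inferred: the article gives a difference of 136.7 ng/mL without an SD, and 18 per group at 90% power implies an SD near 126.5 (136.7/126.5 = 1.08).

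**The case against.** **The path may seldom be taken.** A reader might infer that Friedman is likely to be used because serum markers and PCR values are usually skewed. The documents do not support that. The first description tries a log transformation before any non-parametric test, and lognormal data are normal after logging. In simulated samples of 46, a Kolmogorov–Smirnov test without correction for the estimated mean and SD flagged about 0% of logged lognormal samples; with the Lilliefors correction the figure is about 5% per variable. If the Friedman sentence is read alone and the test is applied to raw values, the uncorrected test flags roughly 10% to 48% (log-SD 0.5 to 0.8) and the corrected one 66% to 96%. The article does not say whether a correction applies, and its two sentences do not settle which order governs. The frequency is therefore open.

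**The 70% is not the trial's error rate.** It is conditional on reaching the fallback and on a drift of 0.5 SD that has no source in the article. At 0.2 SD it is 17%, and with no drift it is nominal. This objection stands, which is why a range is given.

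**The main analysis is untouched.** The repeated-measures analysis with a baseline covariate is stated separately, and this point does not show it to be invalid. Nor does it give grounds for replacing the normality check or analysing every marker on the log scale: those are separate and milder matters of preference.

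**The wording elsewhere is general.** The plural reference to non-parametric tests could be said to leave room for a between-arm test. That does not rescue the sentence, because Friedman is the only one named. An unseen analysis plan might name a suitable test, but the article has not left the matter open. It names a specific test for a purpose that the test cannot serve.

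**Conclusion.** The sentence is wrong as written. In a two-arm parallel trial with two measurements per patient, the Friedman statistic has no arm term and no baseline adjustment, so an outcome analysed with it has no valid comparison of vitamin D with placebo. That follows from the formula and rests on no assumed drift, correlation or distribution.

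The practical size depends on assumptions. At 16 per arm and correlation 0.6, false rejection by the pooled test runs from about 5% (no drift) through 17% (0.2 SD) to 70% (0.5 SD), and a true 1 SD difference made of opposite movements is detected in about 3%. All of these are conditional on the fallback being used. The defect lies in a contingent branch, but that branch is open to all seven primary outcomes.

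**What to change.** Replace the Friedman sentence with:

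> *If an outcome remains clearly non-normal after log transformation, the arms will be compared by rank analysis of covariance (Quade) of the week-12 value on the baseline value.*

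This also removes the ambiguity about whether log transformation comes first. The Mann-Whitney test on change is an acceptable alternative, but one test should be chosen and fixed in advance. The change costs one sentence and no patients, visits or assays. Because the plan has the analyses done blind, before the treatment codes are opened, the test can be fixed while still blind.
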